### Power analysis

A power analysis was performed using G*Power (version 3.1.9.4). Because capillary-fiber perimeter exchange index (CFPE) is a widely measured variable and an important component of anticipated adaptations, we used the results from Kim et al.[27] to power this study. They observed significantly greater CFPE with LHT vs CON (d > 1.5). We used a more conservative, d = 1.2 (reduced by 20%), because older adults might have a blunted response to LHT. We used the statistical analysis of Aim 1 to power the study because it involves more groups (three) and thus requires the largest number of participants. The one-way ANOVA with three groups (d = 1.2, f = 0.4899, α = 0.05) will require 45 total participants (15 per group) to achieve 80% power. This will be followed by two non-orthogonal planned contrasts (CON vs. LHT, LHT vs. HIIT). These *t*-*t*ests (d = 1.2, α = 0.05/2 [Bonferroni]) also require 15 participants per group to achieve 80% power. In the statistical analysis of Aim 2, only two of the three groups are included, leading to greater statistical power. The planned *t*-*t*est (d = 1.2, a = 0.05, 15 participants per group) will achieve 89% power. If needed, the one-way ANOVA with two groups (d = 1.2, a = 0.05, 15 participants per group) will also achieve 89% power. Comparing this number of participants per group to previously published work examining LHT and SKM mitochondria, capillarization, and size [26–28], 15 participants per group is a comparable estimate of sample size. Although not identical to our proposed work, sample sizes of 10 (within-subjects) [23] and 18 (9 per group, between-subjects) [31] were sufficient to detect improvements in glycemic control in overweight men and in obese women with polycystic ovarian syndrome, respectively, in response to whole-body heat therapy. Our power analysis and previously published research support a target sample size of 15 participants per group (CON, HIIT, and LHT). Accounting for a potential 18% attrition rate, we aim to enroll 18 participants per group (9 men, 9 women) for a total target enrollment of 54 participants.

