#### Muscle biopsy.

Following assessment of body composition, a SKM sample is collected using sterile technique and a suction-modified Bergström biopsy needle [43]. The biopsy leg is randomized and counterbalanced across groups. At each testing time point, muscle biopsies will be obtained from a distinct site on the *vastus lateralis* (VL), each separated by 3 cm. The primary biopsy site (used at T1) is located at the anatomical midpoint of the vastus lateralis, defined as the midpoint between the greater trochanter and the lateral border of the patella. The second site (used at T2) is located 3 cm proximal to this midpoint, and the third site (used at T3; LHT and CON groups only) is located 3 cm distal to the midpoint. After disinfecting the area with povidone-iodine, lidocaine without epinephrine is injected subcutaneously at the incision site above the VL, followed by a deeper injection directly into the VL muscle beneath the incision site. A small incision is then made using a #11 scalpel blade to penetrate the skin and fascia over the VL muscle. A suction-modified Bergström needle (5 mm) inserted through this entry point is used to collect approximately 200 mg of VL muscle tissue. Muscle is then quickly cleaned of excess blood and fat, and portioned into sections that will be flash frozen for protein and enzyme analyses, OCT-embedded and frozen in liquid nitrogen-cooled isopentane for histochemistry, formalin-fixed (zinc-buffered formalin; Z-fix) for histochemistry, or fixed in 2.5% glutaraldehyde + 1% paraformaldehyde in phosphate buffer, pH 7.4 for electron microscopy. Immediately following the biopsy, 10 minutes of direct pressure is applied, followed by incision site closure using an adhesive bandage. Pressure dressing is applied over the bandage and participants are instructed to leave this dressing on for at least three hours. Research staff provide participants with biopsy care instructions and contact each participant approximately 24 hours post-biopsy to inquire about potential adverse events and to remind them to contact study personnel if any adverse events occur within the subsequent 72 hours.

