### Statistical analyses

All outcome measures at T1, T2, and T3 will be summarized using descriptive statistics. The study evaluates treatment efficacy by analyzing changes across three distinct time points (T1, T2, and T3). While the data are longitudinal, the primary aims focus on the magnitude of change within specific intervals. Therefore, the magnitude of change between time points for each outcome measure will be calculated for analyses.

To achieve Aim 1 (comparing LHT with CON and LHT with HIIT; k = 3), changes between T1 and T2 values (i.e., before and after Phase 1) for all muscle architecture outcomes, glycemic control outcomes, and frailty risk indicators will be calculated and checked for the assumption of normality using the Shapiro-Wilk test. An appropriate transformation will be conducted if normality is violated. Then, one-way ANOVA with three groups (CON, HIIT, LHT) will be run. This will be followed by two non-orthogonal planned contrasts (CON vs. LHT, LHT vs. HIIT). The Bonferroni correction will be used to control the familywise error rate.

To achieve Aim 2 (comparing LHT with CON after participants in both groups undergo HIIT during Phase 2 of the study; k = 2), changes between T2 and T3 values for all muscle architecture outcomes, glucose tolerance outcomes, and frailty risk indicators will be calculated and checked for the assumption of normality using the Shapiro-Wilk test. An appropriate transformation will be conducted if normality is violated. Then, a *t* test will be run to compare CON and LHT, and confidence intervals will be constructed to compare each variable between the two treatment groups. If improvements for participants in the LHT group from T1 to T2 make the absolute change from T2 to T3 smaller, we will also compare the combined improvements across both phases for the 2 treatment groups. Changes between T1 and T3 in muscle architecture outcomes, glucose tolerance outcomes, and frailty risk indicators will be calculated and transformed if needed. ANOVA analyses will be run and confidence intervals constructed to compare the combined improvements of each factor between the two treatment groups (CON and LHT). We can also employ a one-way ANCOVA for the T2-to-T3 analysis, including the T1-to-T2 change score as a covariate. This ANCOVA method can clarify the relationship between early-phase response and late-phase progress.

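### The optional Aim 2 ANCOVA cannot show how early response relates to later progress, because the shared T2 value biases the covariate slope

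*Protocol article*

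**What the plan says.** The Statistical analyses section of the protocol article works with change scores throughout: "the magnitude of change between time points for each outcome measure will be calculated for analyses". For Aim 2 the stated test is a t test of the T2-to-T3 change, LHT against CON, with confidence intervals. Two supplements follow.

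- The first is conditional: "If improvements for participants in the LHT group from T1 to T2 make the absolute change from T2 to T3 smaller", the arms are also compared on the T1-to-T3 change.
- The second is optional: "We can also employ a one-way ANCOVA for the T2-to-T3 analysis, including the T1-to-T2 change score as a covariate". Its purpose is given in the next sentence: "This ANCOVA method can clarify the relationship between early-phase response and late-phase progress".

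The section does not mention that T2 is part of both changes. It does not mention measurement error or regression to the mean, and it proposes no correction. Only interaction analyses are labelled exploratory.

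For muscle outcomes, the Muscle biopsy section adds: "At each testing time point, muscle biopsies will be obtained from a distinct site on the" vastus lateralis. The sites are the midpoint at T1, 3 cm proximal at T2 and 3 cm distal at T3.

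**The concern.** The covariate is T2 minus T1 and the outcome is T3 minus T2. A participant whose T2 reading happens to be too high appears to have gained more in Phase 1 and less in Phase 2, by the same amount. A participant whose T2 reading is too low shows the reverse. This produces a negative association between the two changes without any biological link.

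Aim 2 asks whether a period of heat therapy makes participants respond better to later exercise. A negative slope would naturally be read as a ceiling, or as heat responders gaining less from exercise. The section already anticipates smaller Phase 2 change after Phase 1 gains, so a reader would be inclined to accept that reading. The model could be run on many muscle, glycemic and frailty outcomes. The same artefact would then recur and look like replication.

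**Working it through.** **The plan's own figure.** The article gives no figure for the slope. The nearest figure is the power of the Aim 2 t test: "d = 1.2, a = 0.05, 15 participants per group) will achieve 89% power". A two-sided noncentral t calculation with those inputs gives 88.7%, so the figure reproduces. The same 15 per group and two-sided 0.05 level are used below.

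**Model.** Let D1 and D2 be a participant's true changes in Phase 1 and Phase 2. Each visit value carries an independent error of variance s2. Then, within arm:

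- covariate = D1 + e2 - e1, with variance Var(D1) + 2·s2
- outcome = D2 + e3 - e2
- covariance of the two = Cov(D1, D2) - s2
- slope = [Cov(D1, D2) - s2] / [Var(D1) + 2·s2]

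Without error the slope would be Cov(D1, D2)/Var(D1). Error pulls it toward -0.5. That is a downward bias for every true slope above -0.5, including zero and all positive values.

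**No true relation.** With Cov(D1, D2) = 0 and the SD of true change equal to k times the error SD, the slope is -1/(k² + 2). The stated ANCOVA (arm plus T1-to-T2 change) was simulated with 15 per arm. The article gives no reliability figures, so k is an assumed range.

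| k | Slope by formula | Significantly negative (nominal 2.5%) |
|---|---|---|
| 0 | -1/2 = -0.50 | about 81% |
| 0.5 | -1/2.25 = -0.44 | about 69% |
| 1 | -1/3 = -0.33 | about 43% |
| 2 | -1/6 = -0.17 | about 14% |

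Repeat simulations agreed to within about 3 percentage points.

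**More participants do not help.** The Power analysis section says: "Accounting for a potential 18% attrition rate, we aim to enroll 18 participants per group". If all 18 per group were analysed, the slope test (two-sided, nominal 5%) would reject in 89% of trials at k = 0 and 51% at k = 1. With 15 per group the figures are 82% and 42%. The bias stays the same and is estimated more precisely.

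**A true positive relation can be hidden.** Take a true correlation of +0.5 between the phase changes, with both true-change variances equal to s2. The error-free slope is +0.5. The expected slope is (0.5 - 1)/(1 + 2) = -0.17, and it was significantly negative in 15% of simulated trials.

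**Where the error comes from.** For biopsy outcomes, s2 includes person-specific variation between sampling sites. A site difference common to all participants goes into the intercept and does not affect the slope. The duplicate and triplicate measurements in the article reduce assay error, but not site or day-to-day variation.

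**The case against.** The strongest reply is that little rests on this analysis. It is worded as a possibility, Aim 2 is powered on the t test, and no slope hypothesis or decision rule is stated. The sentence about clarifying the relationship might mean an arm comparison adjusted for early change rather than a slope to be reported. The section also has another route for the ceiling question, the T1-to-T3 comparison, which contains no T2 value. All of this limits the weight of the point. It does not make the sentence correct: if the analysis is run and read as described, it does not answer the question set for it.

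Four stronger readings are tempting, and the article does not support them.

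- A reader might infer that the main Aim 2 comparison is compromised. The t test and the T1-to-T3 comparison do not use this slope. The adjusted arm difference from the same ANCOVA is a separate question and is not part of this point.
- A reader might take -0.5 and about 81% as the expected result. They hold only if true change does not vary between participants. At k = 1 the rate is already below one half.
- A reader might say that the slope is nothing but noise at T2. The true covariance of the two changes is in the numerator, so the slope is biased rather than empty.
- A reader might count the whole effect of moving the biopsy site as error. Only its person-specific part counts.

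**Conclusion.** The concern holds as a defect in the stated interpretation of an optional, supplementary analysis. Using "a one-way ANCOVA for the T2-to-T3 analysis, including the T1-to-T2 change score as a covariate" makes T2 enter both sides with opposite signs, and nothing in the article corrects for it. The direction of the bias follows from algebra. Its size depends on reliability, which the article does not give: over the assumed range the slope under no true relation runs from about -0.50 to -0.17, and false significant negative results from about 81% to 14%. These figures rest on independent errors of equal variance at the three visits, 15 analysed per arm and a two-sided 0.05 test. Noise will differ between biopsy, glycemic and functional outcomes, so no single figure applies to all of them.

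**What to change.** Delete the sentence on clarifying the early-late relationship. Alternatively, keep the ANCOVA and state that the slope of a change on the preceding change in the same measure is biased by the shared T2 value, and will not be interpreted as evidence of a ceiling or an inverse relation. For the combined effect, rely on the T1-to-T3 comparison between arms that the section already provides for.

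Two additions are possible, each with limits.

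- A cross-measure association, for example the T1-to-T2 change in CFPE with the T2-to-T3 change in VO2peak and arm in the model, could be added as exploratory. It answers a different question and is imprecise at n = 30. Because the two tests fall 2 to 3 days apart in the same testing period, a temporary state of the participant could still affect both.
- An error-corrected slope should be used only where the within-visit error variance can be estimated. The assay and section replicates described do not allow this for biopsy-site variation, since no second biopsy at a visit is described.

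The cost is one or two sentences of analysis text. No new data, sample size change or change to the main tests is needed.

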## Discussion

Frailty and type 2 diabetes mellitus (T2D) are increasingly burdensome health issues for older adults. While exercise training is a cornerstone for managing metabolic diseases, adherence to exercise can be challenging in this population [9,16,17] due to compromised oxygen delivery and mitochondrial dysfunction [19]. Similar to whole-body heat therapy, short-term local heat application has been shown to promote mitochondrial health and preserve or improve capillary density, muscle size, and strength in younger adults [26,27,29,70]. Therefore, the overarching goal of this clinical trial is to examine how local heat therapy improves muscle architecture, glycemic control, and subsequent exercise adaptations, thereby decreasing risk for frailty and metabolic disease progression in older adults with prediabetes.

SKM metabolic function is dysregulated in T2D and is associated with alterations in muscle architecture, including mitochondrial dysfunction [71–73], reduced capillarization [5,6], and decreased SKM mass [7,8]. Notably, mitochondrial dysfunction also appears to underlie decreased capillarization in adults with cardiometabolic disease [74], potentially compromising the capillary network including in SKM. Greater muscle capillary density provides a larger muscle-to-blood exchange area for oxygen diffusion into SKM to support mitochondrial function [75]. Moreover, the SKM capillary network accounts for about 70–90% of insulin-mediated glucose disposal [76,77]. Improved capillarization as an adaptation to exercise training contributes to improved exercise capacity [78]. In contrast, decreased exercise capacity in individuals with T2D can be partially explained by capillary rarefaction [79] and thus reduced peripheral oxygen extraction [80]. These impairments not only contribute to glycemic dysregulation in T2D but also play a role in the loss of SKM mass by limiting nutrient and oxygen delivery necessary to maintain metabolic activity (CITE). Ultimately, this decline in muscle mass and quality leads to reduced function and contributes to the development of phenotypic frailty (CITE). In older adults at risk for T2D, mitochondrial dysfunction and impaired oxygen delivery may contribute to exercise intolerance, which can lead to decreased exercise participation and adherence [19], further elevating the risk of developing T2D and related complications.

Studies in both humans and rodent models suggest that whole-body heat therapy enhances mitochondrial function, muscle capillarization, glycemic control, and muscle fiber CSA, even in the absence of structured exercise training. With whole-body heat therapy, fasting glucose and insulin decreased in sedentary, overweight men (34–39°C for 1–6 hours, 10 sessions) and obese rats (38°C for 30 min, 3 times per week for 12 weeks) [22–25]. In contrast, 3 or 6 weeks of whole-body heat did not correct the glucose dysregulation in a Type I diabetic (T1D) model [81]. Al Sabagh et al. speculated that the specific models used (obese, at risk for T2D vs T1D) may explain the discordant findings [81]. Still, 6 weeks of whole body heat therapy was able to alleviate SKM mass loss and attenuate functional decreases in the T1D model [81].

While whole-body heat therapy modalities such as sauna and hot water immersion show promise, they may not be practical for widespread use. Studies using LHT (e.g., shortwave diathermy, hot water circulation) demonstrate similar benefits to those observed with whole-body heat therapy [70,82]. Applying shortwave diathermy 2 hours per day for 6–10 days to raise the IM temperature by approximately 3–4°C increased mitochondrial biogenesis and attenuated muscle atrophy in young sedentary men and women [26,70]. Heating the thighs alone using hot (48–52°C) water to raise leg skin temperature to 39–40°C without altering core temperature increased vascular endothelial growth factor (*VEGF*) and angiopoietin 1 mRNA expression [29], consistent with improved angiogenic capacity. However, mitochondrial density did not change with these heat therapy settings [21]. Other work using a single 4-hour local heat application that only raised the IM temperature to ~36.3°C (average skin temperature of 37.3°C) also reported no changes in mitochondrial gene expression [82], suggesting that there may be a higher threshold for heat-induced SKM mitochondrial adaptations. These results suggest that by understanding how heat elicits specific physiological adaptations and refining LHT settings accordingly, LHT can be an alternative therapeutic approach. However, shortwave diathermy and hot water circulation apparatuses remain costly, making these modalities of heat delivery less accessible for widespread use. Therefore, the clinical trial described herein will test the efficacy of LHT using affordable heat pads as a standalone intervention to improve SKM architecture, glycemic control, and decrease frailty risk, and as a means of preconditioning SKM to improve exercise adaptations among older adults with prediabetes.

## Conclusions

The HEAT Study will be the first to determine the impact of using affordable local heat pad therapy on SKM architecture, glycemic control, and frailty risk and to explore how these changes may enhance skeletal muscle adaptations to exercise training in older adults with prediabetes. Findings from this study will expand our understanding of physiological effects of local heat therapy, and biospecimen analyses will provide evidence for mechanistic insights. These data will inform parallel mechanistic studies to undercover therapeutic targets. Most importantly, findings will provide foundational evidence to include local heat pad therapy in clinical recommendations to combat metabolic disease progression and frailty risk in older adults, potentially transforming clinical practice, and ultimately reducing the health burden of T2D and frailty.
